### Intervention

Forty ambulatory patients with KOA are randomly assigned to receive Tai Chi (n = 20) or attention control (wellness education and stretching) (n = 20) in twice-weekly one-hour group sessions for 12 weeks (Figure 1).

### Tai Chi

The Tai Chi program is based on the classical Yang Style [19] with some modifications as described below. Patients participate in two 60-minute Tai Chi sessions conducted weekly for 12 weeks. Each session includes: 1. warm up and review of Tai Chi principles and techniques; 2. Tai Chi exercises; 3. breathing techniques; and 4. various relaxation methods. The teachings are carried out by a Tai Chi master (RR) who has over 20 years experience conducting Tai Chi Mind-Body exercise programs. Several modifications are developed by the Tai Chi master to achieve the physical (body) and mental (mind) goals of the study for KOA, accommodate KOA symptoms and limit dropouts. For example, we eliminate the 90 degree knee-flexor joint stance used in the traditional Tai Chi exercise that would place stress on the knees and replace it by having patients rest their backs on the wall to strengthen the quadriceps muscles and also by performing sitting and standing exercises from a chair. Patients perform 2 sets: one with the legs together and one with legs apart to further strengthen various muscles around the knee. In addition, the ability to tap into the power of the mind is developed further by having patients perform visualizations while sitting on the edge of a chair. Subjects are instructed to practice Tai Chi at least 20 minutes a day at home and encouraged to maintain their usual physical activities, but not to participate in additional new strength training other than their Tai Chi exercises.

### Attention control (wellness education and stretching)

We use a wellness education and stretching program for the control group because this approach has been successfully used in other studies [18,20-22]. The program provides an active control for the attention being paid to the Tai Chi group. There is adequate personal contact with the subjects (for attention) with little anticipated effect on the main outcomes. The control groups also attend two 60-minute sessions per week for 12 weeks. Each session starts with 40 minutes of didactic sessions on 1) OA knowledge; 2) diet and nutrition; 3) therapies to treat OA; and 4) physical and mental health education (recognizing and dealing with stress and depression, etc). The final 20 minutes of the hourly session consists of stretching exercises involving the upper body, trunk and lower body, each stretch being held for 10 to 15 seconds. Subjects are also instructed to practice at least 20 minutes of stretching exercises per day at home. All subjects are encouraged to maintain their usual physical activities, but not to participate in additional strength training other than their class stretching exercises. Throughout the 12-week period, we track the number of and reasons for any missed sessions in both groups.

### Measurements

The Osteoarthritis Research Society currently recommends a core set of 4 domains (pain, physical function, patient's global assessment, and, for studies of at least 1 year, joint imaging) for outcome measurement for assessing KOA in clinical trials [17,23]. This core set is used in this study (except for joint imaging). Every participant is evaluated at baseline (prior to starting either intervention), after completing the intervention (12 weeks later), and at a 24 week and 48 week follow-up (see Table 1).

**Table 1 T1:** Sequence of trial measurements for primary and secondary outcomes*

**VISIT**	**Baseline**	**Intervention** (for 12 weeks)**	**Week 12**	**Week 24 Follow up**	**Week 48 Follow up**
**Time (months)**	**-1**	**0**	**1 – 3**	**6**	**12**
**Primary outcome measure**					

WOMAC-Pain	X	X	X	X	X

**Secondary outcome measures**					

**WOMAC-Physical function**	X		X	X	X
**WOMAC-Stiffness**	X		X	X	X
**Physicians' Global KOA Severity**	X		X	X	X
**Patients' Global KOA Severity**	X		X	X	X
**SF-36 & EQ-5D & CES-D**	X		X	X	X
**Self-efficacy**	X		X	X	X
**Outcome Expectation**	X		X	X	X
**Social Support**	X		X	X	X
**Enjoyment Questionnaire**	X		X	X	X
**Physical Functional Tests*****	X		X	X	X
**Physical Activity Questionnaire**	X		X	X	X
**Joint Proprioception**	X		X	X	X
					
**Medications**	X	X	X	X	X
**Adverse Events**		X	X	X	X
**Body Mass Index**	X		X	X	X
**Weekly Update**		X			
**Knee X-Ray**	X				
**Adherence**		X	X	X	X
**Follow-up Questionnaire**				X	X

* KOA = Knee Osteoarthritis, WOMAC = Western Ontario and McMaster Universities Osteoarthritis Index, SF-36 = Medical Outcome Survey Short-Form 36, EQ-5D = EuroQol self-repot questionnaires, CES-D = Center for Epidemiology Studies Depression index.

** Randomization to Tai Chi or Attention Control intervention.

*** Physical Function Tests include range of motion, standing balance, 6-minute walk, and chair standing.

#### Global knee pain

The degree of self-reported global knee pain and function is recorded using the WOMAC index [24]. The WOMAC is a self-reported instrument used to assess lower extremity pain, stiffness and physical function. The primary endpoint of the study is the change in the pain subscale of the WOMAC between baseline and the 12-week assessment.

In addition, the physician provides a global score summarizing both knees using a visual analog scale version at baseline and follow up. In the baseline assessment, we use a self-reported knee-specific global pain visual analog scale (VAS) with range 0–100 mm to compare pain severity in each knee. In the event that an enrollee has identical pain scores in both knees, our statistician randomly assigns one of these to be the 'study knee' (see statistical analysis). The 'study knee' will be the knee on which primary outcome assessments are determined and used for analysis of strength outcomes.

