### Sample size

Our empiric sample size is guided by numbers and outcomes of an RCT conducted at Tufts University that tested an exercise intervention among older adults with KOA [18]. That study enrolled 46 patients and randomized them to either 4-month home-based progressive strength training or an attention control group of similar duration. The results were that the strength training group experienced a 36% decrease in the WOMAC index pain subscale (the primary outcome) compared to an 11% decrease in the attention control group. Thus, the exercise group had a mean change in the WOMAC pain score of -79 (SD = 91), while the control group had a mean change of -20 (SD = 77). Based on those numbers, a sample size of 20 per group and alpha = 0.05, would have power of 60% to detect a between-group difference of -59.0. While we recognize that the study is underpowered for a definitive comparison, we are primarily concerned with gathering preliminary data in order to plan and evaluate this innovative research direction.

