### Statistical Analysis

The primary outcome is the measurement of change in knee pain between baseline and 12 weeks. Secondary outcomes are measurements of change at 24 weeks and 48 weeks. These will be analyzed both as individual time points and in longitudinal analyses. Analyses will be intention-to-treat with secondary analyses based on completers.

We will also explore a knee-based approach to the study that will use linear mixed models to adjust for correlations in outcome between knees. The most disabled knee will be used as the unit of analysis. One knee will be chosen at random if two knees are equally affected. Considering both knees would require accounting for the correlation between knees and for the presence of disability in only one knee for many participants. However, we will characterize individuals on the basis of unilateral vs. bilateral KOA and explore any possible influences of this characterization in secondary analyses.

For the patients who withdraw during the study, every effort will be made to complete a follow-up WOMAC and clinical knee examination at the time of withdrawal. If a withdrawal assessment cannot be made, we will carry forward the last assessment of knee pain, physical function or as a conservative assessment to bias towards the null hypothesis.

We will also perform a cost-effectiveness analysis to evaluate whether Tai Chi is a cost-effective therapy for patients with KOA. The costs will be estimated from health care utilization reported by subjects at the end of the trial using the Health Assessment Questionnaire that includes medication usage, hospitalization and health care professionals' visits. The differences in direct and indirect health care cost between the Tai Chi and attention control (wellness education and stretching) groups will also be compared.

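### The 60% power rests on an unadjusted comparison of change in WOMAC pain and no baseline adjustment is named; stating one would probably gain precision for one degree of freedom

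*Protocol article*

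**What the plan says.** The article defines the primary endpoint twice. Under Global knee pain: "The primary endpoint of the study is the change in the pain subscale of the WOMAC between baseline and the 12-week assessment". Under Statistical Analysis: "The primary outcome is the measurement of change in knee pain between baseline and 12 weeks". Both name an outcome variable. Neither names a test, a model or a covariate.

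The Sample size section takes its planning values from an earlier exercise trial: "the exercise group had a mean change in the WOMAC pain score of -79 (SD = 91") and "the control group had a mean change of -20 (SD = 77"). From these it concludes that "a sample size of 20 per group and alpha = 0.05, would have power of 60" per cent "to detect a between-group difference of -59.0". It is open about the limitation: "While we recognize that the study is underpowered for a definitive comparison, we are primarily concerned with gathering preliminary data".

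The Statistical Analysis section covers intention-to-treat and completer analyses, single time points and longitudinal analyses, carrying forward of missing values, and an exploratory knee-based mixed model. Baseline adjustment is neither planned nor excluded. The article gives no SD of WOMAC pain at a single visit and no correlation between visits.

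**The concern.** An unadjusted comparison of change forces the coefficient of the baseline score to equal 1. Unless the true slope of week-12 pain on baseline pain is 1, this leaves removable noise in the treatment contrast. The baseline WOMAC pain score is available on everyone, because the Randomization section requires the baseline assessment to be complete before an envelope is opened.

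The trial has 20 per arm and says itself that it is underpowered, so precision that needs no further patients is worth having. It matters equally for the stated aim of preliminary data, since a narrower interval is a better basis for planning the next trial. The Discussion says that follow-up is complete and the analysis is still to come. The sample size can no longer change, but the analysis can still be stated in advance.

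**Working it through.** **Inputs.** From the Sample size section: mean change -79 (SD 91) and -20 (SD 77), difference 59, n = 20 per arm, alpha 0.05. Sidedness is not stated. Assumed here, because the documents do not give them: the correlation ρ between baseline and week-12 WOMAC pain, and equal SDs at the two visits.

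**Step 1: reproduce the stated power.**
- Pooled SD = √((91² + 77²)/2) = √7105 = 84.29.
- Standard error of the difference = 84.29 × √(2/20) = 26.66.
- 59/26.66 = 2.213, and 2.213 − 1.960 = 0.253, which gives power 60.0% (two-sided, normal approximation). This matches the stated 60%.
- The one-sided normal figure would be 71.5%, so the stated value is two-sided.
- With the noncentral t on 38 df, the same inputs give 57.8%. This is the reference for the comparisons below, so that both sides use one method.

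**Step 2: is adjustment compatible with the endpoint?** Write change as Y12 − Y0 = a + b·arm + c·Y0 + error. Adding Y0 to both sides gives Y12 = a + b·arm + (c + 1)·Y0 + the same error. The treatment effect b and its standard error are identical. Adjusting for baseline therefore leaves the endpoint as it is.

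**Step 3: the gain with equal SDs.** If σ is the SD at each visit, the variance of change is 2σ²(1 − ρ) and the adjusted residual variance is σ²(1 − ρ²). Their ratio is (1 + ρ)/2, so the adjusted SD is 84.29 × √((1 + ρ)/2), with 37 df. The 95% half-width is t × SD × √(2/20), with t = 2.024 on 38 df or 2.026 on 37 df.

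| Analysis | SD | Power for 59 | 95% half-width |
|---|---|---|---|
| Unadjusted change | 84.3 | 57.8% | 54.0 |
| Adjusted, ρ = 0.3 | 68.0 | 76.2% | 43.5 |
| Adjusted, ρ = 0.5 | 73.0 | 70.2% | 46.8 |
| Adjusted, ρ = 0.7 | 77.7 | 64.7% | 49.8 |
| Adjusted, ρ = 0.8 | 80.0 | 62.3% | 51.2 |
| Adjusted, ρ = 0.9 | 82.2 | 59.9% | 52.6 |

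**Step 4: how firm is this?**
- *Estimating the slope with chance baseline imbalance.* Inflating the variance by 1 + 1/36 takes off about one point of power: 75.1%, 69.0%, 63.5%, 61.1% and 58.8% at the five correlations. At ρ = 0.95 the result is 57.7%, so the gain has gone.
- *Unequal SDs.* Let k be the week-12 SD divided by the baseline SD, holding the SD of change at 84.3. At ρ = 0.5, k = 0.8 gives 81% and k = 1.2 gives 64%. At ρ = 0.7 and k = 1.2 it is 59%.
- *Direction.* In units of the baseline variance, the change-score variance minus the adjusted variance is (1 + k² − 2ρk) − k²(1 − ρ²) = (1 − ρk)². This is never negative. Adjustment cannot raise the residual variance, and its benefit vanishes only as the slope ρk approaches 1.

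**The case against.** The strongest objection is that the article fixes a variable and not a model. A reader might infer from the two endpoint sentences that the trial is committed to raw, unadjusted change. The documents do not support that: neither sentence says unadjusted, and Step 2 shows that the proposed model fits the wording. Nor does powering on change-score SDs bind the analysis. Those were the SDs the planning study supplied, and using them is conservative if an adjusted analysis follows. A full protocol or analysis plan that is not shown may already adjust, and silence in a condensed article is not an error in itself. All of this stands. What remains is that unadjusted change is the only comparison for which the article gives a basis, and a more precise one is available within the same endpoint.

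A reader might also take a rise from 58% to 70% as the expected gain. That holds only at ρ = 0.5 with equal SDs, and the article gives neither. The article's own figure is 60%; 57.8% is the t-based value of the same calculation.

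Three further arguments are tempting but should not be used.
- The entry threshold does not make regression to the mean a special problem. It is only > 40 on a scale of 0 to 500, and it applies equally to both arms.
- Baseline means back-calculated from the planning study's percentage changes rest on an assumption about what those percentages refer to, and they say nothing about imbalance in this trial.
- Chance imbalance does not bias the unadjusted contrast on average, because allocation is random. At ρ = 0.5 the SD at each visit is also 84.3, so a one-standard-error baseline difference is 26.7 points and moves the change contrast by half of that, about 13 points or 23% of 59. That is a reason to adjust, but it does not show that imbalance could account for most of the target.

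**Conclusion.** The point holds as a recommendation on the analysis. The stated 60% is correct as calculated, and it is the power of an unadjusted comparison of change. No baseline adjustment is named, and none is excluded. Adding baseline WOMAC pain as a covariate would, under equal visit SDs, raise t-based power by roughly 5 to 18 points for correlations from 0.8 down to 0.3 (62.3 − 57.8 = 4.5; 76.2 − 57.8 = 18.4). It would shorten the interval half-width by about 3 to 10 points. The direction is secure. The size is not, because it depends on an unreported correlation and on the ratio of the two visit SDs, and it shrinks to nothing as the slope approaches 1. Even at the favourable end of the equal-SD range, power stays below 80%, so the article's description of the trial as preliminary still applies.

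**What to change.** State, before outcomes are compared by arm, that the primary analysis is a linear model of change in WOMAC pain from baseline to week 12 (or, equivalently, the week-12 score) on arm, with baseline WOMAC pain as covariate. Report the adjusted difference with its 95% confidence interval. Use the same form for each continuous secondary outcome with its own baseline value, and keep the unadjusted change as a supportive display. If an analysis plan already says this, the article need only refer to it. If an adjusted power figure is quoted, give the assumed correlation and a range.

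The cost is a sentence or two of text and one degree of freedom (37 instead of 38), plus about one point of power for chance baseline imbalance, which the figures in Step 4 already include. The endpoint, the data collected and the sample size stay as they are.

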#### Radiographs

Anterior-posterior (AP) and lateral standing knee radiographs are obtained at the initial screening examination (the baseline assessment) using the Framingham study protocol [25] and are screened by the study rheumatologist (RK) for acceptance criteria. AP knee radiographs are also obtained with the patient in the fully extended standing position and lateral images with the patients in the supine position with the knee in 30 degrees of flexion, as previously suggested [26,27]. The study rheumatologist (RK) and a musculoskeletal radiologist independently screen the radiographs using the Kellgren and Lawrence (K/L) grading system for global tibiofemoral radiographic severity, and discrepancies are resolved with a third reviewer (TM). The K/L score is determined for each knee compartment based on osteophyte formation, joint space width, and subchondral bone scleroses [28]. All scores reported are for the most severely affected knee (study knee).

#### Knee examination

Knee examination is performed at baseline and during each follow up visit. The study rheumatologist (RK), who is blinded with respect to the patient's treatment assignments, assesses the presence and severity of the knee joint abnormalities relevant to KOA. The knee examination components were selected based on recent data demonstrating the potential for reproducibility across examiners [27]. The study rheumatologist examines for swelling and tenderness of the knee joint and asks each subject to rate pain on a scale of none, mild, moderate or severe. The examination sequence is as follows: 1. Palpate study knee joint swelling (bulge sign, balloon test and patellar tap); 2. Palpate for patella tendon tenderness; 3. Palpate for patella tenderness; 4. Palpate for anserine bursa tenderness; 5. Palpate for popliteal space tenderness; 6. Rate pain in the knee/knee joint when limb is in motion; 7. Scale the general crepitus sign as none, fine or coarse; 8. Palpate for tibiofemoral tenderness laterally; 9. Palpate for tibiofemoral tenderness medially. Evidence of inflammation (e.g. joint effusion), joint deformity, and joint contractures will also be noted. Assessment of the patient's global status is also performed.

#### Range of motion (flexibility)

The passive range of motion for both knees (at full extension and flexion) is measured with a plastic goniometer (Whitehall Manufacturing, model G300,) marked in 1 degree increments. Patients are positioned on their sides with the lower extremity to be examined resting on a stabilizing board. The fixed arm of the goniometer is placed to align with the femur, pointing towards hip joint and the other arm in alignment with the fibula. With one hand holding the goniometer and supporting the leg, taking care to maintain axis of goniometer with knee axis, patients are asked to flex and extend their leg as far as they can. The maximal degrees of full flexion and extension are then read and recorded.

#### Knee joint proprioception

Knee proprioception, which is reduced in KOA [29], is measured using a Biometrics™ electrogoniometer with an ADU301 angle display unit during each assessment visit. Three test angles (30, 45 and 60 degrees) are evaluated with each subject in a sitting position taken as neutral (0 degree). The electrogoniometer is placed longitudinally in alignment with the femur and tibia with a double-sided medical tape and used to determine each of the three test angles. Patients are first shown one of the angles, which is held for a few seconds, then they are asked to close their eyes and attempt to reproduce the angle; this is repeated for all three test angles.

#### Physical performance

Physical performance assessments include the timed stand, standing balance and 6 minute walk tests. Timed stand tests measure time taken to complete ten full stands from a sitting position [30]. This is a measure of lower extremity muscle power. Patients are instructed to complete chair stand time as quickly as possible and are timed to the nearest 0.001 seconds. The same chair is utilized for testing before and after the interventions. Patients begin the chair stand seated with their arms folded across their chests, then rise to a standing position and sit back down with their back against the back rest of the chair. The test is completed when the patient stands for the 10^th ^repetition. Chair stand time is recorded using the best (lowest) score of 2 trials.

The standing balance tests include tandem, semi-tandem, side-by side, and one-legged stands. Patients are asked to maintain each position for 30 seconds. For each task, the research staff first demonstrates the task, asks the patient if they feel comfortable and ready and then supports the patient while positioning themselves [31-33]. One point is given if they exceed 30 seconds and none if they can not do or do not attempt the test.

The six minute walking test is a reliable measure of functional exercise capacity [34]. Patients are asked to walk as fast and as far as possible within the 6-minute period and are accompanied by the research staff using a wheel measure (Redi measure, Redington, Windsor, CT) that measures distance covered in inches. Patients are given verbal encouragement throughout the 6 minutes and are informed of the remaining time throughout the 6 minutes. The distance covered at the end is noted and recorded.

#### Health Related Quality of Life (HRQL)

HRQL assessments are made using the Medical Outcome Study Short Form 36 (SF-36) [35], and the EuroQol (EQ-5D) [36] instruments. The SF-36 measures 8 domains: physical functioning, role-physical, bodily pain, general health, vitality, social function, emotional health and mental health. The EQ-5D measures 5 dimensions: mobility (disability), self-care (disability), usual activities (handicap), pain/discomfort (impairment), and anxiety/depression (impairment). There is also a visual analogue thermometer rating scale to evaluate the overall patient perception of health on a 0 to 100 scale. Higher scores indicate a better health state.

#### Depression

The Center for Epidemiology Studies Depression (CES-D) index is used to assess depressive symptoms [37]. It includes a 20-item Likert-type scale with scores ranging from 0 to 60. Higher scores indicate greater dysphoria.

#### Outcome expectation

Outcome expectations are beliefs that carrying out a specific behavior such as physical activity will lead to a desired outcome. The brief outcome expectations scale (OES) [38] contains questions that ask about physical and mental benefits and will be used to assess outcome expectations. The measure is scored by summing the ratings for all the items and dividing by 9 to get the average of all 9 items. Scores can range from 1 to 5, with 1 indicating low outcome expectations for the exercise and 5 suggesting high outcome expectations.

